## Abstract

**Background:**

Depression and anxiety frequently emerge during late adolescence and young adulthood; however, many conventional and app-based interventions struggle to sustain engagement. Virtual reality (VR) exergaming, music-based activities, and social interaction each show promise for supporting young people’s mental health, but their combined therapeutic value remains insufficiently tested.

**Objective:**

This study aims to evaluate the effectiveness of a 6-week VR-based social musical exergame for reducing depressive and anxiety symptoms in young adults. The secondary objectives are to explore whether changes in basic psychological need satisfaction are associated with symptom change and to assess the effects on loneliness, presence, cardiorespiratory fitness, and in-game music-movement synchronization.

**Methods:**

This study is a 3-arm, parallel-group randomized controlled trial. A total of 110 participants aged 18 to 25 years with mild to moderate depression or anxiety will be recruited and randomized in a 1:1:1 ratio to (1) a VR social musical exergame, (2) a matched VR solo musical exergame active control, or (3) a waitlist control receiving standardized mental health guidance. Assessments will be completed at baseline, at the postintervention assessment (week 6), and at the 1-month follow-up assessment (week 10). The primary planned comparison is the experimental group vs the active control group.

**Results:**

This study was approved by the ethics committee of Hunan Traditional Chinese Medical College on September 8, 2025 (YXLL202509006) and prospectively registered at ClinicalTrials.gov on March 15, 2026 (NCT07482852). Internal institutional funding had been secured. As of April 2026, the trial status was “not yet recruiting;” no participants had been enrolled, and no data analysis had been conducted. Recruitment is anticipated to begin in May 2026, with primary completion on March 1, 2028, study completion on May 1, 2028, and publication of the primary findings expected in late 2028.

**Conclusions:**

This protocol describes a self-determination theory–informed, multicomponent VR intervention designed to evaluate whether adding a bundled social layer to a matched solo exergame improves short-term mental health outcomes. The trial is expected to provide initial evidence on efficacy, safety, and potential mechanisms while generating hypotheses for future dismantling and longer-term trials.

**Trial Registration:**

ClinicalTrials.gov NCT07482852; https://clinicaltrials.gov/ct2/show/NCT07482852

**International Registered Report Identifier (IRRID):**

PRR1-10.2196/83737

## Introduction

### Background and Rationale

Late adolescence and young adulthood (ages 18-25 years) represent a high-risk window for the onset of mental health disorders, with a large proportion of lifetime conditions first emerging by the mid-20s [1-4]. Depression and anxiety in this developmental period are shaped by interacting social, psychological, and biological processes and remain a substantial public health concern [5-7].

However, conventional interventions such as counseling and health education often struggle to sustain participation, and this limitation extends to many digital mental health tools. Even when mental health apps are widely available, long-term engagement remains low, suggesting that motivational design is a persistent implementation challenge [8-10].

The convergence of immersive technologies and psychologically informed intervention design offers a promising alternative. Virtual reality (VR) can deliver embodied and engaging exergaming experiences [11-16], music can support emotional regulation and social bonding [17-19], and socially shared or synchronized activity may reduce loneliness and enhance connectedness [20-28]. Although VR-based mental health interventions have shown encouraging results for distress reduction [22,29-32], these components have often been studied in isolation. To address this gap, this trial is informed by self-determination theory (SDT), which proposes that autonomy, competence, and relatedness are basic psychological needs linked to intrinsic motivation and well-being [33,34]. Importantly, this intervention is designed as a bundled SDT-informed intervention rather than an experimental test of each need in isolation. The study therefore evaluates the effectiveness of a multicomponent social VR musical exergame and explores whether changes in need satisfaction are associated with symptom change; these exploratory analyses are hypothesis generating and do not permit causal conclusions about individual SDT mechanisms.

### Objectives

#### Primary Objective

The primary objective of this study is to determine the effectiveness of a 6-week VR social musical exergame intervention in reducing symptoms of depression and anxiety in young adults, compared with a matched active control group and a waitlist control group.

#### Secondary Objectives

The secondary objectives of this study are as follows:

To explore whether changes in basic psychological need satisfaction are associated with changes in depression and anxiety symptoms. These analyses are specified as exploratory and hypothesis generating rather than as definitive tests of temporal mediation.To explore whether in-game performance (ie, music-movement synchronization) moderates competence satisfaction and mental health outcomes as an exploratory secondary analysis.To assess the intervention’s effects on loneliness, sense of presence, and cardiorespiratory fitness.

## Methods

### Study Design

This study will use a 3-arm, parallel-group, single-center randomized controlled trial design. Assessments will be conducted at baseline (T0), immediately after the intervention (T1, week 6), and at a 1-month follow-up (T2, week 10) to evaluate short-term maintenance of effects. The primary planned comparison is the experimental group vs the active control group, which isolates the added value of the social layer over a matched solo VR intervention. Comparisons involving the waitlist control are secondary. This protocol was prepared in accordance with the SPIRIT (Standard Protocol Items: Recommendations for Interventional Trials) guidelines.

### Study Setting

Participants will be recruited from local universities, vocational colleges, and community health centers in Changsha, China.

### Recruitment

Recruitment strategies will include posters and flyers at universities, vocational colleges, and community centers; online announcements; and referrals from collaborating educational and community services.

### Participant Timeline

Following screening and informed consent, eligible participants will complete baseline assessment (T0), undergo randomization, receive the 6-week intervention or waitlist condition, complete the postintervention assessment at week 6 (T1), and complete the follow-up assessment at week 10 (T2; Table 1).

**Table 1 table1:** Schedule of enrollment, interventions, and assessments.

Time point	Enrollment	Allocation	T0^a^	T1^b^	T2^c^
Eligibility screen	✓				
Informed consent	✓				
Randomization		✓			
Intervention			✓		

^a^T0=baseline: week 0.

^b^T1=posttest: week 6.

^c^T2=follow-up: week 10.

### Participants

A total of 110 young adults aged 18 to 25 years will be recruited. The eligibility range was narrowed to 18 to 25 years to improve developmental homogeneity and align the sample with late adolescence and emerging adulthood, a period marked by elevated risk for depression and anxiety [1-4]. The participant eligibility criteria are shown in Textbox 1. Participants will be recruited through advertisements at local universities, vocational colleges, and community health centers.

Participant eligibility criteria.
**Inclusion criteria**
Aged 18 to 25 yearsMeeting criteria for mild to moderate depression (Beck Depression Inventory-II score: 14-28) or anxiety (Beck Anxiety Inventory score: 8-25)
**Exclusion criteria**
A diagnosis of a severe mental illness (eg, psychosis) or an acute psychiatric crisis requiring immediate treatmentSignificant virtual reality (VR) motion sickness or other contraindications to safe VR participationCurrent engagement in other forms of systematic psychotherapy

### Sample Size Calculation

An a priori power analysis was conducted using G*Power. On the basis of meta-analyses of related VR-based mental health interventions [30,31], a medium effect size (f=0.25) was assumed. To achieve 80% power at an alpha level of .05 for the primary group-by-time comparison, a required sample of 90 participants was indicated. To account for an anticipated attrition rate of 20% to 30%, consistent with rates reported in VR intervention literature, the recruitment target is set at 110 participants. A sensitivity analysis indicates that with 30% attrition (leaving approximately 77 participants), statistical power for the primary comparison would be reduced to approximately 70%, which is acknowledged as a limitation. To minimize attrition, the study will implement flexible scheduling, session reminders, brief mid-study check-ins, and graduated VR exposure in the first session to identify and manage cybersickness early. If observed attrition exceeds 30%, this will be reported transparently and considered in the interpretation of results. This sample size determination was made for the primary clinical outcomes and was not specifically powered for mediation or moderation analyses; those analyses will therefore be treated as exploratory.

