#### Active Control Group: VR Solo Musical Exergame

This group will engage in a VR exergame with the same frequency, duration, exercise intensity, game content, and music design as the experimental group. However, all social features will be disabled. This condition is designed to preserve autonomy and competence support while removing the bundled social layer, and it serves as the primary comparator for testing the unique contribution of social interaction.

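### The protocol gives no reason why f=0.25, taken from meta-analyses of VR-based interventions, applies to social versus solo VR, so the stated power is unsupported for the primary contrast

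*Protocol article*

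**What the plan says.** The Sample Size Calculation section gives the effect and its source: "On the basis of meta-analyses of related VR-based mental health interventions [30,31], a medium effect size (f=0.25) was assumed". It continues: "To achieve 80% power at an alpha level of .05 for the primary group-by-time comparison, a required sample of 90 participants was indicated". It adds that 30% attrition would leave about 77 participants and reduce power for the primary comparison to about 70%.

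Study Design defines that comparison: "The primary planned comparison is the experimental group vs the active control group, which isolates the added value of the social layer". The solo arm receives a VR exergame "with the same frequency, duration, exercise intensity, game content, and music design as the experimental group", with the social features switched off, and "it serves as the primary comparator for testing the unique contribution of social interaction". The modelling text under Data Management repeats the choice: the planned primary contrasts are experimental versus active control at weeks 6 and 10. Waitlist contrasts are secondary.

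On prior evidence, the Background and Rationale says of VR, music and shared activity that "these components have often been studied in isolation", and the abstract says that "their combined therapeutic value remains insufficiently tested". The limitations in the Discussion describe the trial as powered for its primary clinical outcomes. They do not mention where the effect size came from.

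**The concern.** VR, music, movement and dose are common to both arms of the primary comparison, so whatever they contribute cancels. What remains is the increment from the social layer. The effect used for sizing is justified by literature described only as VR-based mental health interventions, and the article does not link that literature to social versus solo VR.

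The 80% and 70% figures tell a reader how much weight a null result can bear. If the solo arm already delivers part of the benefit, the difference between arms could be well below the assumed effect. A non-significant result could then be taken, on the strength of a published 80%, as evidence that social interaction adds nothing. The trial is meant to inform later dismantling studies, so that misreading would carry forward.

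**Working it through.** **Inputs from the protocol article.** f = 0.25, alpha .05, 80% power, N = 90, about 70% at N = 77 (Sample Size Calculation); allocation 1:1:1 (Randomization and Blinding); primary contrast experimental versus active control (Study Design). Per arm this is 90/3 = 30, and 77/3 ≈ 26.

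**Assumptions, because the article does not state them.** Two-sided test; f read as the standardised difference between two equal groups, d = 2f = 0.50; correlation ρ between baseline and follow-up scores of 0.5 or 0.7 for baseline-adjusted analyses.

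**Step 1: the plan's own figure.** For a group-by-time F test with k groups and m measurements, noncentrality is λ = f²·N·m·ε/(1−ρ), where ρ is here the correlation among repeated measures. With f = 0.25, alpha .05, 80% power and ε = 1, the required N is:

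| Groups × times | ρ = 0 | ρ = 0.5 |
|---|---|---|
| 3 × 3 | 69 | 36 |
| 3 × 2 | 81 | 42 |
| 2 × 3 | 54 | 28 |
| 2 × 2 | 66 | 34 |

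None is 90. The figure 90 does appear under settings that the article does not state, for example 3 × 3 with ρ = 0 and ε = 0.65, or a between-groups test of 2 groups at 2 times with ρ = 0.4. That between-groups set-up gives about 74% at 77 participants, not 70%. The stated 80% therefore cannot be reproduced from what is printed. That is a separate matter, but it means the 80% is not a secure base for further scaling.

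**Step 2: what is being compared.** In the primary contrast both arms receive the VR exergame, and only the social features differ. No section argues that f = 0.25 suits that difference.

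**Step 3: two-arm contrast at its actual size.** Noncentral t with 2n − 2 degrees of freedom and noncentrality δ = d·√(n/2)/√(1−ρ²), with ρ = 0 for the unadjusted analysis.

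- d = 0.50, n = 30: δ = 0.50·√15 = 1.936, power 48%. With ρ = 0.5, δ = 1.936/0.866 = 2.236, power 59%. With ρ = 0.7, δ = 1.936/0.714 = 2.712, power 76%.
- d = 0.375 (75% of the assumed effect), n = 30: δ = 1.452, 1.677 and 2.034; power 30%, 38% and 52%.
- d = 0.25 (50%), n = 30: δ = 0.968, 1.118 and 1.356; power 16%, 20% and 27%.
- d = 0.50, n = 26: δ = 1.803, 2.082 and 2.524; power 42%, 53% and 70%.

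The 75% and 50% fractions are assumptions. The documents give no estimate of the social increment.

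**Step 4: the effect of size alone.** Take the plan's 80% as given and treat the test as a two-sided 1-df contrast. Its noncentrality is 1.960 + 0.842 = 2.802. At 75% of the effect this becomes 2.101, with power 56%; at 50% it becomes 1.401, with power 29%. Because λ scales with f², halving the effect needs about four times the sample in any set-up. This step shows sensitivity only.

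**The case against.** A reader might infer that the plan was sized on one comparator and tests another. The documents do not establish that. The article does not say what the two meta-analyses used as comparators; they may have included active or even VR controls. The supportable statement is that the link is not made.

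A reader might also infer that the true power is low because the social increment must be smaller than a whole-VR effect. No section shows this. The social layer is a substantial bundle: at least 10 minutes of team tasks and 5 minutes of open voice chat per session. Unblinded self-report could also enlarge the observed difference. Nor do the background statements say that evidence on a social increment is absent. They say that components have often been studied separately and that the combination is under-tested, and the Introduction cites work on shared activity.

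The article does call the effect assumed. It describes the trial as preliminary and acknowledges about 70% power under heavy attrition. This softens the risk of misreading, but none of it addresses the source of the effect size. Full power tables can reasonably be left to a longer document. However, the article itself prints the effect, its source and the resulting power for the primary comparison, so the lack of a link between them is a flaw in what is stated, not an omission.

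**Conclusion.** The concern holds in limited form. The 80% and 70% figures are unsupported for social versus solo VR, because the only justification offered for f = 0.25 is literature on VR-based interventions in general and nothing connects it to the increment under test. This rests on the wording of the article, not on the content of references 30 and 31.

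No specific lower power is demonstrated. The Step 3 range depends on reading f = 0.25 as d = 0.5, on a two-sided test, on 30 per arm and on the assumed correlations. Within those assumptions the two-arm contrast falls short of 80% even at the full assumed effect, and far short at half of it. The point is separate from whether 90 reproduces and from whether 110 covers the stated attrition; it would remain if both were resolved.

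**What to change.** In Sample Size Calculation, state that f = 0.25 is a working assumption for social versus solo VR and is not derived from evidence on that contrast. Keep the target of 110. Restate power for the two-arm experimental-versus-active contrast at its actual per-arm size, for the assumed effect and for smaller ones such as 75% and 50% of it, and give the within-person correlation used. Amend the limitations statement that the trial is powered for its primary clinical outcomes so that it agrees. Add that a non-significant social-versus-solo result will be interpreted by its confidence interval and not as evidence of no added value.

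These are text changes. They need no further participants and no change in conduct, and the article reports that no one had been enrolled as of April 2026. The downside is a less favourable stated power.

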### Data Management

All data will be entered into a secure electronic database with verification procedures. Identifiable information will be stored separately from outcome data on encrypted institutional servers, accessible only to authorized members of the research team.

For the primary outcomes, linear mixed-effects models will be used to examine group, time, and group×time effects on BDI-II and BAI scores. Separate models will be fitted for depression and anxiety outcomes, with participant-level random intercepts to account for repeated measures over time. Gender and primary presenting concern (the stratification variables) will be included as covariates, and baseline symptom severity will be considered in model specification as appropriate. The primary planned contrasts will compare the experimental group with the active control group at T1 and T2; comparisons involving the waitlist control group will be secondary and should be interpreted with caution, given the expectancy and novelty confounds inherent in waitlist comparisons. Post hoc pairwise comparisons will be adjusted for multiple testing using a Holm procedure. Secondary outcomes will be analyzed using analogous mixed-model approaches. Cybersickness (SSQ scores) will be examined as a potential covariate in sensitivity analyses to assess whether differential simulator sickness across groups confounds the primary results. Missing data assumptions will be examined, with maximum likelihood estimation in mixed models as the primary approach and multiple imputation and per-protocol analyses used as sensitivity analyses where appropriate. Exploratory analyses will examine whether changes in Basic Psychological Need Satisfaction Scale scores are associated with changes in BDI-II and BAI scores and whether music-movement synchronization moderates selected outcomes; these analyses will be interpreted as hypothesis generating rather than confirmatory causal tests.

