The protocol also has important limitations that should be considered when interpreting future results. First, the 1-month follow-up captures only short-term stability rather than long-term remission; it cannot assess relapse patterns, sustained behavioral change, or long-term clinical trajectories, and future trials should include follow-up periods of at least 3 to 6 months. Second, the social condition is a bundled manipulation that combines voice chat, collaboration, competition, and visible performance comparison; therefore, the trial cannot isolate the independent effect of each social feature, and the study should be understood as a preliminary multicomponent efficacy trial that may inform future dismantling or factorial designs to identify active therapeutic ingredients. Third, the primary outcomes (BDI-II and BAI) are self-report measures administered in an unblinded trial, which increases susceptibility to expectancy, demand characteristics, and placebo effects, particularly given the immersive and novel nature of the VR intervention; future trials should consider incorporating clinician-administered measures (eg, the Hamilton Depression Rating Scale) or objective biomarkers alongside self-report instruments. Fourth, although the intervention is informed by SDT, the bundled design does not isolate or manipulate autonomy, competence, and relatedness independently; any associations between need satisfaction and symptom change are therefore exploratory and cannot establish causal mediation. Fifth, differential cybersickness between the social and solo VR conditions could confound group comparisons, as more complex social interactions may elicit different levels of simulator sickness. Sixth, the study is powered for the primary clinical outcomes but not specifically for mediation or moderation analyses, which are therefore exploratory and hypothesis generating. Finally, although the eligibility range has been narrowed to 18 to 25 years to reduce developmental heterogeneity, individual differences within this developmental period may still influence intervention response.

If the intervention demonstrates favorable short-term effects and acceptable safety, the findings may support a scalable and engaging digital mental health approach that is feasible on consumer-grade VR hardware. The protocol may also inform future dismantling studies that test specific social features, as well as trials with longer follow-up and broader multisite implementation.

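### The 80% power quoted for 90 participants is not supported for the declared primary comparison, which uses only two of the three arms

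*Protocol article*

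**What the plan says.** Under Sample Size Calculation, the Protocol article says that "a medium effect size (f=0.25) was assumed" and then: "To achieve 80% power at an alpha level of .05 for the primary group-by-time comparison, a required sample of 90 participants was indicated". The recruitment target of 110 is built from that 90. The same section adds that "with 30% attrition (leaving approximately 77 participants), statistical power for the primary comparison would be reduced to approximately 70" percent.

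Study Design says: "The primary planned comparison is the experimental group vs the active control group". Comparisons with the waitlist are secondary. The analysis text under Data Management repeats the choice: "The primary planned contrasts will compare the experimental group with the active control group at T1 and T2". Randomization and Blinding gives 1:1:1 allocation over three arms.

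The limitations in the Discussion say that "the study is powered for the primary clinical outcomes", and confine the lack of power to the mediation and moderation analyses.

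**The concern.** The power statement and the primary comparison do not refer to the same set of participants. The 90, the 110 and the 77 all count three arms, and one of those arms plays no direct part in the primary contrast. A power figure for a three-arm total cannot be carried over to a two-arm contrast without recalculation.

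What is at stake is how a null result is read. A reader told that the primary comparison has 80% power would take a non-significant difference between social and solo VR as fair evidence that the social layer adds little. If the true power for a medium difference is well below 80%, that reading is too strong.

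**Working it through.** **Inputs from the article.** f=0.25, alpha .05, 80% power, N=90, target 110, and 77 retained at 30% attrition (110 × 0.7 = 77), all from Sample Size Calculation. Allocation is 1:1:1. The primary contrast is experimental versus active control at T1 and T2.

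**Inputs assumed.** Two-sided testing; correlation r between visits, shown over a range; and, for the two-arm illustration, d=0.5 at one visit. For two equal groups f = d/2, so f=0.25 corresponds to d=0.5.

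**Step 1: does 90 reproduce for a group-by-time test?** For the within-between interaction with k groups and m visits, the noncentrality is λ = f²·N·m/(1−ρ), with (k−1)(m−1) and (N−k)(m−1) degrees of freedom. The smallest N for 80% power with three groups is:

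| Visits | ρ=0.5 | ρ=0 |
|---|---|---|
| 3 | 35 | 67 |
| 2 | 42 | 81 |

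None of these is 90. At ρ=0.5 with three visits, N=90 gives λ = 0.0625 × 90 × 3 / 0.5 = 33.75 and power above 99%. A one-way three-group test needs 158. A value of 90 does appear for a three-group test of the average over three visits at ρ of about 0.34. That correlation is not stated, and the test is neither a group-by-time test nor the two-arm contrast.

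**Step 2: how many participants enter the primary contrast?** 90 × 2/3 = 60, or 30 per arm. 77 × 2/3 = 51.3, or 25.7 per arm. The 90 cannot mean the two compared arms alone, because the 110 derived from it is the whole trial.

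**Step 3: illustrative power at one visit.** Use the noncentral t with 2n−2 degrees of freedom and δ = [d/√(1−r²)]·√(n/2), where r is the correlation of baseline with outcome and r=0 means no adjustment. At n=30 and r=0, δ = 0.5 × √15 = 1.94. At r=0.5, δ = (0.5/0.866) × 3.873 = 2.24. At r=0.7, δ = (0.5/0.714) × 3.873 = 2.71.

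| Baseline adjustment | 30 per arm (stated 80%) | 25.7 per arm (stated about 70%) |
|---|---|---|
| none | 48% | 42% |
| r=0.5 | 59% | 53% |
| r=0.6 | 66% | 59% |
| r=0.7 | 76% | 69% |
| r=0.75 | 82% | 76% |

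If the contrast is instead a simple difference in change from baseline, the variance factor is 2(1−r). Power at 30 per arm is then 36%, 48% and 69% at r=0.3, 0.5 and 0.7.

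**Step 4: T1 and T2 averaged.** With baseline adjustment, equal correlations and d=0.5 at both visits, the variance factor is (1+r)/2 − r². At r=0.5 this is 0.50, which gives 77% at 30 per arm and 70% at 25.7. At r=0.6 it is 0.44, which gives 82% and 75%.

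**Step 5: size needed or difference detectable, single visit.** For 80% power at d=0.5, the contrast needs 64 per arm unadjusted (192 over three arms) or 49 per arm at r=0.5 (147), before attrition. With 30 per arm, the difference detectable with 80% power is d=0.74 unadjusted and 0.64 at r=0.5.

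**The case against.** The best defence is that the two-arm percentages rest on assumptions that the article does not make. It names a group-by-time test, and f in that test is not half a between-arm d at one visit. Applied literally to two arms with N=60 and ρ=0.5, the interaction formula gives 97% to 99% power. A strong baseline correlation, or averaging the two follow-up visits, also brings power close to or above the stated 80% and 70%. Finally, the article describes the trial as preliminary and admits lower power under attrition, and an article may leave software settings to the fuller protocol.

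Much of this stands, and it limits the claim. A reader might infer that the true power is 48% to 59%, or that a real benefit would be missed about half the time. The documents do not support that as a fact, because they fix neither the two-arm effect nor the correlation. A reader might also infer that alpha is split between the two symptom scales. The text applies Holm only to post hoc pairwise comparisons, so no lower alpha is used here. Nor is an unstated software setting an error in itself.

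The defence does not rescue the stated figures. The literal interaction convention implies a difference in change of about 1 SD in a two-visit design, and it would not have produced 90. The planned contrasts read most naturally as separate ones at T1 and T2, not as an average. Baseline adjustment, on which the higher figures depend, is left open under Data Management. If the three-arm calculation is taken at its word, so that 90 gives exactly 80%, the same f and per-person information in the two primary arms gives about 72% with 60 participants and about 64% with 51. The attrition caveat concerns dropout, not the number of arms.

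**Conclusion.** Wrong as written. That the stated power rests on a three-arm total while the primary contrast uses two arms follows from the article's own text and needs no assumption. That 90 does not follow from the printed inputs, under the usual settings for the test named, is supporting evidence.

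The size of the shortfall is conditional. With d=0.5 at one visit, two-sided alpha .05 and 30 per arm, power reaches 80% only when the baseline correlation is about 0.75, or when T1 and T2 are averaged with a correlation of about 0.6. The result does not show that the trial must be larger. It shows that the article gives no basis for 80%, or for about 70% at 77, for the comparison it calls primary.

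One further caution concerns the effect size. The article takes f=0.25 from meta-analyses of VR-based interventions in general, whereas both arms of the primary contrast receive VR. What those meta-analyses compared cannot be checked from the article, so nothing more is claimed.

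**What to change.** Rewrite the power paragraph for the experimental versus active-control contrast as it will be tested: at T1 and T2 separately, averaged, or at whichever visit is named primary. Give the number per arm, the assumed SD and between-visit correlation, whether baseline is adjusted for, and the alpha. Alternatively, state the difference detectable with 80% power at the planned size per arm.

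Remove the 80% and 70% figures, or label them as applying to an omnibus three-arm test with its settings stated. Amend the Discussion sentence that calls the study powered for its primary outcomes so that it agrees. Note beside the effect size that its source is VR interventions generally, while both primary arms receive VR.

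The cost is one paragraph and one sentence of rewording, and a less favourable stated power. No extra participants are needed, and recruitment had not begun as of April 2026.
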